### Recruitment {15}

#### Aim 1

Stakeholders will be identified by the study team and will include individuals who are expected to interact with or be impacted by the CACP program, e.g., potential referring clinicians, members of the health care team (e.g., case managers), CPs, and hospital administrators. Individuals will receive an email informing them of the study and requesting their participation in an interview. Those who respond and indicate interest will be scheduled for an individual interview to be conducted in person or by videoconference. Participants will complete oral consent prior to the interview.

#### Aim 2

Patient identification, enrollment, and consent procedures will be consistent with the pragmatic point-of-care study design and objectives to ensure feasibility within the real-world practice. Consistent with the point-of-care trial approach, the study team will disseminate information about the CACP program and trial to ambulatory, ED, and hospital practices. Clinicians as well as case managers and social workers (who oversee discharge planning in the inpatient and ED settings) will be encouraged to refer patients to the CACP program if this would allow patients to leave the hospital sooner or avoid hospitalization in the first place. The patient’s clinical care team will therefore identify patients for consideration of enrollment into the CACP program based on the patients’ clinical situation and needs. Case managers, social workers, and clinicians will be able to refer patients to the CACP program using established clinical workflows for home health and other post-hospital care programs. Such referrals will automatically result in a notification to the CP team; the CP team will verify clinical eligibility and CACP program capacity. If the request can be accommodated by the CACP program and the program has census capacity for that request, the CP team will then notify the study research team, who will approach the patient for enrollment and informed consent. After informed consent is obtained, the study team member will randomize the patient 1:1 to CACP versus usual care and notify both the CP service and the referring service of the outcome of randomization. If the CACP program has no capacity to accept patients, the referring service will be notified immediately upon the referral. The referring service will then make alternative care plans. This process is analogous to home health agency referrals in the hospital system.

Patients who refuse participation in the CACP trial may be eligible to receive CP services outside of the trial if the number of non-trial patients receiving CP care at that time would be at or below the CACP program capacity prior to the launch of the trial and dedicated CP staffing to support trial activities. In the Rochester location, there was capacity for an average of 1 patient per day (because CPs care for other lower acuity non-trial patient populations as well), while in the Wisconsin location, there was no capacity prior to the trial as the CACP program did not exist there prior to the trial. Patients who consented to participate in the trial but were randomized to usual care will not be able to opt out and request enrollment in the CACP program outside of the trial. However, all patients who complete 30 days of follow-up within the trial will be able to receive CP services after the 30-day period irrespective of their initial randomization allocation. Patients who consented to participate in the trial and were randomized to the CACP arm, and who were hospitalized within their 30-day follow-up period, will be able to receive CP services again upon discharge if clinically appropriate.

#### Aim 3

Patient participants who were randomized to the CACP arm will be contacted by telephone to offer participation in the interview after their last CP visit. Three contact attempts will be made. To ensure diversity of perspectives, the study team will review potential interview participants each week and identify recruitment priorities based on diversity in terms of age (< 50 and ≥ 50 years old), gender, race and ethnicity, rurality, referral geography (WI and MN), diagnosis for which they were referred, referral site (pre-hospital setting or ED or hospital), and whether the patient has an assigned Mayo Clinic PCP.

All CPs who provided CACP care during the trial will be invited by email to participate in an interview. We will also contact a purposive sample of clinicians who referred patients to the CACP program, along with administrators and other members of the health care team for interviews. Referring clinicians will be sampled based on their service line, location (clinic or ED or hospital; Minnesota or Wisconsin), and number of patients referred to the trial. Three contact attempts will be made. Additionally, all CPs, clinicians whose patients were cared for in the CACP study arm, members of the health care team who interacted with the CACP program, and select administrators will receive a survey via email at the end of the trial to seek their feedback on the CACP program. Members of the health care team who interacted with the program will be identified based on data from the CP referral tracker, as well as a review of orders in the EHR.

### Assignment of interventions: allocation

#### Sequence generation {16a}

Individuals will be block randomized 1:1 at the patient level to usual care or to CACP per a computer-generated randomization schedule stratified by source of referral (pre-hospital versus ED versus hospital) and location (Minnesota versus Wisconsin) using blocks of random sizes.

#### Concealment mechanism {16b}

The Remote Electronic Data Capture (REDCap) database software will be used for allocation concealment. The system does not release the randomization code until the participant is enrolled in the trial.

#### Implementation {16c}

The randomization algorithm will be generated by an analyst within REDCap. Stratification factors create six stratum levels as the product of categories of each factor (two geographic locations and three referral sites). Randomization is performed separately within each stratum level, utilizing blocks of random size, based on the schema entered by the data analyst. This sequence is blinded to the individuals entering the patients into the data collection tool. When the patient is identified, consents, and is ready to randomize, the information is entered into the REDCap system with randomization schema, a randomization button is pressed, and REDCap returns the next allocation in the sequence for given strata.

### Assignment of interventions: blinding

#### Who will be blinded {17a}

Participant and care team blinding is not possible in this trial. Study team members collecting qualitative and survey data collection cannot be blinded to study allocation. The statistician will provide unblinded data to the DSMB. The adverse event adjudication team will be blinded to study allocation, though members will have access to the patient’s EHR where CP notes may or may not be present for a given patient. We will use a group nomenclature (group 1 and group 2) during data analysis. The data will be unblinded for appropriate interpretation before publication. Analysis of quantitative data will be performed at the close of the study.

#### Procedure for unblinding if needed {17b}

Neither clinicians nor patients will be blinded to allocation, such that no unblinding will occur.

### Data collection and management

#### Plans for assessment and collection of outcomes {18a}

Participants randomized to CACP will have access to CP services ordered and overseen by the treating clinical team per the current standard of care. Thus, the clinical trial evaluates the CACP care delivery model rather than the clinical care that is provided to patients within it. Participants randomized to usual care will not have access to CP services and will continue with their care as planned by the treating clinician(s).

All participants will complete a baseline survey at the time of enrollment/consent and at 30 days. Participants randomized to CACP will also complete a survey after their last CP encounter. Paper copies of the baseline surveys will be completed at the time of enrollment or provided to the participant and returned by mail. In the CACP treatment arm, we will ask that baseline surveys be completed and returned before or during the first CP visit. In the usual care arm, for participants who did not complete their baseline survey at the time of enrollment, up to 3 reminder phone calls will be made by a member of the research team to participants who have not returned their survey by the end of week 1.

Participants randomized to the CACP treatment arm will also be asked to complete a survey after their last CP visit. This survey will be handed to the participant by the CP at their last visit with a pre-stamped envelope so it can be completely private and returned by mail or sealed and given to the CP for delivery. If participants need help completing the survey, the research team study coordinator will contact them by telephone and complete the survey with them. Patients in the intervention arm who are recruited and consent to participate in an interview will complete it by telephone with a trained member of the study team unaffiliated with intervention delivery. Interviews will be audio-recorded with permission and transcribed for analysis.

Patients in both arms will be asked to complete a paper survey at day 30, administered between days 30 and 40 (first attempt) and with all 3 contact attempts completed by day 90. If participants need help completing the survey, it can be done over the phone with the research team study coordinator.

The EHR will be queried at 30 days, 6 months, and 12 months for ED visits, hospitalizations (excluding planned hospital admissions for scheduled surgeries, procedures, and/or treatments), and other outcomes of interest not collected directly from the patient. The study setting includes two hospital systems with the same Epic EHR and the ability to view records regardless of event location; therefore, we anticipate high completeness of EHR data for this trial. However, we will supplement these data as needed with patient-reported information about ED visits and hospitalizations, ascertained in the 30-day survey and confirmed with phone follow-up.

We will also survey clinicians and other members of the health care team who referred participants enrolled in the CACP intervention arm, administrators involved with the CACP program, and community paramedics and interview purposive samples of clinicians, administrators, and community paramedics. These surveys will be completed using a web-based survey platform. Survey invitations will be sent by email, and non-responders will receive up to three reminder contacts. Interviews will be conducted in-person or by telephone or video conference, and audio recorded and transcribed for analysis.

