#### Provisions for post-trial care {30}

The need for ancillary and post-trial care is not anticipated as part of this trial. For participants in the intervention arm, the provision of any ancillary care during the trial, including that related to the needs identified by CPs, will be managed and/or compensated using standard patient procedures. After the outcome ascertainment period is completed (day 30), if study participants require CP services, they will be eligible to receive them through the usual clinical care pathway irrespective of study allocation.

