HRQoL (aim 2 secondary)	EQ-5D survey	HRQoL scores (0–100) calculated across five domains	The scores will be summarized using mean, SD, minimum, median, and maximum scores by treatment arm at *T*_3_	Comparison between the groups at *T*_3_ and the day after randomization to *T*_3_
Patient experience with treatment and self-management, i.e., treatment burden (aim 2 secondary)	PETS survey	PETS scores calculated for each domain	Domain scores will be summarized using mean, SD, and minimum and maximum scores	Comparison between the groups at *T*_3_ and the day after randomization to *T*_3_
Patient evaluation of CP care (aim 2 secondary)	Surveys items on involvement in care, communication and health information, caring and concern, and care coordination	Patient-reported CP involvement in care	Percentage of patients who respond “strongly agree” or “agree.”	Descriptive assessment of intervention patients in the CACP program at *T*_2_
Program satisfaction (aim 3 secondary)	Surveys items on program satisfaction	Self-reported satisfaction with CP care and the CACP program	Percentage of respondents who are “extremely satisfied” or “very satisfied.”	Comparison between participant types will be made after enrollment ends
Program satisfaction and recommendations for improvement and sustainability (aim 3 secondary)	Qualitative interviews	Program satisfaction and recommendations on improvement and sustainability	Perspectives on how well the program meets user needs and whether/how it should be continued	*T*_2_ for a sample of patients in the CACP program and after enrollment ends for CPs and referring clinicians

* − T*_*1*_ enrollment, *0* allocation, *T*_*1*_ first CP visit, *T*_*2*_ after last CP visit (note: *T*_2_ can be before or after *T*_3_, depending on the patient’s clinical need and how long they will be receiving CP services), *T*_*3*_ 30 days post-allocation, *T*_*4*_ 6 months post-allocation, *T*_*5*_ 12 months post-allocation

**Table 2 Tab2:** Implementation outcomes

RE-AIM domain	Outcome	Source	Time point

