**Interventions**							
CACP care			X				
**Assessments**^**a**^							
Age, sex, race, ethnicity, comorbidities, medications (EHR)	X						
Social support information (survey)		X					
HRQoL—EQ-5D (survey)		X			X		
Treatment burden—PETS (survey)		X			X		
ED visits, unplanned hospitalizations, death (EHR)					X	X	X
Falls with injury, medication errors with harm					X		
Program experience (survey and interview^b^)				X			

* − T*_*1*_ enrollment, *0* allocation, *T*_*1*_ first CP visit, *T*_*2*_ after last CP visit (note: *T*_2_ can be before or after *T*_3_, depending on the patient’s clinical need and how long they will be receiving CP services), *T*_*3*_ 30 days post-allocation, *T*_*4*_ 6 months post-allocation, *T*_*5*_ 12 months post-allocation

^a^Assessments are interviews, self-report surveys, and EHR (chart abstraction)

^b^Patients in the CACP program will complete a *T*_2_ survey. A sample of patients in the CACP program will be recruited to participate in an interview

Patient participants will be followed for 1 year post-allocation. They will complete surveys at baseline and 30 days; participants randomized to CACP will also complete surveys after their last CP visit. The EHR will be used to ascertain ED visits and unplanned hospitalizations (e.g., excluding planned hospital admissions for scheduled surgeries, procedures, and/or treatments at 30 days, 6 months, and 12 months post-allocation). If patients received CP services as part of usual care between 30 days and 12 months, this will be identified from the EHR and accounted for in the analyses.

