Sensitivity analyses concerning the primary and secondary endpoints will be conducted, including excluding hospice deaths, examining the impact of the number of CP visits, examining the impact of the duration of CP care (< 10 days, 10–19 days, 20–29 days) and per protocol vs ITT. The impact of covariates will be assessed by using multiple linear regression or multiple logistic regression.

Descriptive statistics and figures will be provided as appropriate for secondary outcomes, and baseline demographics will be summarized for each arm. Validated instruments (e.g., EQ-5D) will be scored per official guidance, and the results will be reported as appropriate. When data is available, changes in rates or scores between baseline and 30 days will be reported for each arm along with comparisons between the groups. Implementation outcomes will be summarized using descriptive statistics.

#### Aim 3

Qualitative data will be analyzed following qualitative content analysis procedures, guided by the theoretical constructs employed in the study. Analysis will begin with at least two members of the study team reviewing audio files and transcripts. A coding framework will be developed, starting with a priori topics in the interview guide and constructs from theoretical frameworks like CFIR. Analytic memos will be used to summarize the findings, including any key differences by participant role.

Surveys will be analyzed using descriptive statistics and scoring guidance for validated instruments (e.g., CSAT). Integration of findings will involve a comparison of quantitative and qualitative findings by construct, e.g., survey and interview data on acceptability and sustainability.

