### Methods in analysis to handle protocol non-adherence and any statistical methods to handle missing data {20c}

Primary analyses will be conducted using an intention-to-treat approach. Secondary analysis will be conducted using the per-protocol approach, where patients randomized to the CACP arm who never received the intervention or did not complete the intervention (i.e., did not respond to CP service calls to be scheduled and had to be administratively discharged from the CACP program) will be excluded. Patients randomized to the control condition will not be eligible to receive CP services during the 30-day follow-up period. We will confirm this using an EHR review and exclude any patients who received CP care during that period.

Missing data: For the primary outcome, missing data (e.g., loss to follow-up, withdrawal, death) are expected to be minimal at 30 days, as data are collected from the EHR and are part of the standard of care. Primary analyses will be conducted on the intention-to-treat population. For missingness greater than 20%, multiple imputation will be used.

If patients self-report on *T*_3_ surveys any hospitalizations or ED visits not captured in the EHR, the study staff will confirm those visits using phone follow-up. We will report the percentage of missing data for all primary and secondary outcomes at each time point, as well as for individual survey items. For validated measures with multiple items, we will follow scoring guidance for missing data.

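### EQ-5D and PETS are compared as 30-day outcomes, but survey contacts may run to day 90, after CP services open to usual care, so late responses may dilute the 30-day contrast

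*Protocol article*

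**What the plan says.** All references are to the protocol article.

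- **Nominal time point.** The notes to Tables 1 and 3 define T3 as "30 days post-allocation". Participant timeline {13} says of patient participants: "They will complete surveys at baseline and 30 days".
- **Comparison.** In Table 1 (Outcomes {12}) the time point for both EQ-5D and PETS reads "Comparison between the groups at *T*_3_ and the day after randomization to *T*_3". The statistical methods section {20a} adds that, where data are available, "changes in rates or scores between baseline and 30 days will be reported for each arm along with comparisons between the groups".
- **Collection.** Plans for assessment and collection of outcomes {18a} describes a paper survey at day 30 for both arms, "administered between days 30 and 40 (first attempt) and with all 3 contact attempts completed by day 90".
- **CP access.** The section on non-adherence and missing data {20c} states: "Patients randomized to the control condition will not be eligible to receive CP services during the 30-day follow-up period". Provisions for post-trial care {30} then says: "After the outcome ascertainment period is completed (day 30), if study participants require CP services, they will be eligible to receive them". Recruitment {15} likewise says that patients who complete 30 days of follow-up "will be able to receive CP services after the 30-day period irrespective of their initial randomization allocation".
- **Later CP use.** Participant timeline {13} says that CP services received in usual care between 30 days and 12 months will be found in the EHR and allowed for in the analyses. It does not say how.

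**The concern.** The post-trial care section treats outcome ascertainment as finished at day 30 and opens CP services on that basis. For EQ-5D and PETS, collection only begins then. A form completed on, say, day 80 would enter the comparison labelled as a 30-day value. By then the patient is further from the index episode, and a usual-care patient may have received the intervention.

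Two secondary outcomes are at stake. Treatment burden is named in the secondary objectives {7}, and health-related quality of life is a secondary outcome in {12}. If the between-arm difference fades with time or with CP use in the control arm, pooling early and late responses under one label tends to understate the 30-day difference. It also makes the result harder to interpret, because it averages over an unstated mix of assessment times.

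**Working it through.** The plan gives no figure that depends on survey timing, so there is nothing to reproduce. The check sets the timing statements side by side and then illustrates the possible dilution.

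**Timing**

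| Item | Day | Source |
|---|---|---|
| T3, nominal | 30 | Table 1 note |
| CP services barred for usual care | to 30 | {20c} |
| CP services open to either arm, if required | after 30 | {30}, {15} |
| First survey attempt | 30 to 40 | {18a} |
| Last of three attempts | by 90 | {18a} |

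- Latest first attempt relative to T3: 40 − 30 = 10 days.
- Latest contact relative to T3: 90 − 30 = 60 days.
- Latest contact as a multiple of nominal follow-up: 90 / 30 = 3.

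The whole contact window therefore lies at or after the point where CP access opens to the control arm. Day 90 limits the contact attempts. A form mailed back after the last attempt could arrive later still.

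**Illustrative dilution**

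Let D be the true 30-day difference, f the share of responses that are late (taken as equal in both arms), and r the share of D still present among late responders. Then

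observed difference = D × [(1 − f) + f × r] = D × [1 − f(1 − r)].

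The document gives neither f nor r. Both are assumptions:

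| f | r = 0 | r = 0.5 |
|---|---|---|
| 10% | 90% of D | 95% of D |
| 20% | 80% of D | 90% of D |
| 30% | 70% of D | 85% of D |
| 50% | 50% of D | 75% of D |

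For example, f = 0.30 and r = 0.5 gives 1 − 0.30 × 0.5 = 0.85. The r = 0 column is the extreme case, with no effect left in any late response. Across these assumptions the dilution runs from slight to large, and nothing in the document narrows it.

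**The case against.** A reader might infer that the T3 comparison is not a 30-day comparison at all. The document does not support that. The first attempt falls at days 30 to 40, so responses to it may lie close to T3. Day 90 is the outer limit for repeated contact with people who have not yet answered. Only late responders are affected, and their share is unknown.

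Other points on the plan's side:

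- **Access is not uptake.** After day 30 CP services are available only if required and through the usual clinical pathway. No uptake rate is given.
- **Loss of effect is not documented.** Recovery by two to three months is plausible for these episodes, but the document has no data on it. Table 1 notes that the last CP visit may fall after T3, so CP care, and perhaps its effect, may continue beyond day 30 in the CACP arm.
- **The window is the same in both arms.** A reader might suspect that return times differ by arm, since the trial is unblinded and CACP patients receive an extra survey at their last CP visit. That is conjecture; nothing in the document shows it.
- **Later CP use is to be accounted for.** The sentence in {13} addresses crossover. It stands beside the EHR utilization outcomes, gives no method, and may not extend to the surveys. Even if it does, allowing for CP use does not correct for a score taken well after day 30.
- **An analysis window may be set in the SAP.** Such a rule commonly belongs there, so its absence here is not the criticism. The contact schedule itself is stated here, and an analysis rule would not change it.

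These points limit the size and certainty of the problem. They do not reconcile a 30-day label with contacts permitted to day 90.

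**Conclusion.** The point holds as a mismatch between the stated time point of EQ-5D and PETS and the schedule for collecting them. Contacts may run 60 days past T3, over a period when usual-care patients may receive CP services. Late responses may blur or dilute the 30-day contrast.

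The amount cannot be estimated from the document. The tabulated range of 95% down to 50% of the true difference rests wholly on assumed values for the late share and the retained effect, with equal late shares in the two arms. It shows what could happen and predicts nothing. The document does not support a claim that the 30-day effect is lost, or that the arms are biased against each other by different return times.

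The primary outcome and the 30-day utilization outcomes come chiefly from the EHR and do not depend on when EQ-5D and PETS are completed. The change is worth making because it is cheap and brings these two secondary outcomes into line with their label.

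**What to change.** 1. **Contact schedule.** Keep three contacts, start at day 30, and space them closely on the same schedule in both arms, so that they end soon after T3 (for example by about day 45) instead of day 90.
2. **Data.** Record the completion date of each survey and any CP service received between day 30 and completion.
3. **Analysis.** Pre-specify and report EQ-5D and PETS restricted to surveys completed within that window, alongside the analysis of all returned surveys. Say whether the commitment in {13} to account for later CP use covers these scores and, if so, how.

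Reporting both analyses is preferable to dropping late surveys outright, which would exchange timing error for possible non-response bias.

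The cost is possibly a few fewer returned surveys and one extra analysis, with no added contacts. Recruitment was already under way when the article was written, so the tighter schedule helps only participants not yet surveyed. The restricted analysis can include everyone whose completion date is known.
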